## **1.0 Administrative Information**

***Trial Registration:*** ClinicalTrials.Gov Identifier: NCT0298757

***Funding:*** Canadian Institute of Health Research (CIHR), the Ontario Strategy for Patient Oriented Research, and the Provincial Council for Maternal and Child Health (PCMCH) in Ontario

## 91 **2.0 Introduction**

92

### 93 **2.1 Background and Rationale**

94 Medical and surgical advances have led to falling mortality rates for almost every life-threatening  
95 condition of childhood, such as extreme prematurity (1), complex congenital anomalies (2), and  
96 congenital or acquired brain injury (3). Technologic advances such as ventilator support, feeding tubes  
97 and transplantation have successfully prolonged the lives of children and youth with lung, gut and other  
98 organ failure. This epidemiologic transition (4) has created a burgeoning population of children with  
99 medical complexity (CMC) – children with new morbidities, which are caused by longer survival itself as  
100 well as the complications of the therapies that have prolonged their life expectancy.

101 CMC are defined as “children with chronic conditions with elevated service needs, functional limitations  
102 and high healthcare use” (5). About 0.7% of children are CMC (41,500 in Canada), yet they use a  
103 remarkable one-third of all child health resources (~\$1.1 billion/year in Canada) (6), accounting for 43%  
104 of child deaths, 49% of hospital days, and 75-92% of consumed assistive health technology (7, 8). CMC,  
105 their parental caregivers and families, and the healthcare system that support them endure enormous  
106 challenges, including: multiple and prolonged hospitalizations (9), frequent medical errors (10), poor care  
107 coordination (9, 11), and extraordinary stress on parental caregivers (12). The consequences include poor  
108 caregiver health (13), marital discord (14), and profound negative financial impact (15).

109 Our team has shown through a series of before- and after- studies, that targeted and integrated complex  
110 care interventions may improve the health outcomes of CMC (16), including reducing the extraordinary  
111 burden of caregiving on their families (17) and mitigating costly and unnecessary healthcare expenditures  
112 (18, 19). However, the validity of these findings and those of other investigators has been limited by  
113 small sample sizes, lack of control groups and incomplete outcome measures (20).

114 Within its mandate as a provincial program, and supported by Ontario’s Ministry of Health and Long-  
115 Term Care (MOHLTC), the Provincial Council of Maternal and Child Health (PCMCH) has implemented  
116 the Complex Care Kids Ontario (CCKO) Strategy (**Appendix 1**). CCKO will help improve care for CMC  
117 who are Medically Fragile and/or Technology Dependent (MFTD) and their families by providing an  
118 integrated approach to medical care and coordination. The strategy also aims to improve service delivery,  
119 health, and quality of life of the patient-families involved. Over four years (2016-2020), ~6,200 CMC  
120 across five regions will receive tailored personalized care plans and coordination from a key worker to  
121 complement other integrated care initiatives such as Health Links (21). The five CCKO Regions (four  
122 serving the catchment area of Ontario’s children’s hospitals, and one dedicated to Northern Ontario) will  
123 be established beginning in July 2016 to plan and implement integrated, coordinated healthcare across  
124 Ontario (**Appendix 2**). Each region will be responsible for care coordination across acute care, primary  
125 care, rehabilitation, home and community care providers. This will be facilitated by dedicated key  
126 workers to establish seamless integrated care teams including innovations to: reduce unnecessary

uncoordinated face-to-face appointments with many subspecialists, and develop and maintain a single, comprehensive and collaborative care plan that is designed to meet the child's/family's goals and optimize health outcomes.

## **2.2 Overarching Aim**

The goal of this project is to develop a robust evaluation of the province-wide complex care intervention, CCKO, and test whether dedicated key workers and coordinated patient-family care plans have an impact on improving service delivery and quality of life for CMC and their families. Our primary objective is to evaluate the rollout of CCKO using a randomized wait-list design and mixed-methods (qualitative and quantitative) research.

### **Primary Research Question:**

1. a) What is the comparative effectiveness of the CCKO intervention relative to the waitlisted group?
- b) What are the elements that explain the successes and gaps of the intervention?

**Hypothesis:** We hypothesize CCKO will lead to improved variety of patient- and family-centred outcomes, while decreasing unnecessary healthcare utilization. In particular, we hypothesize that the intervention will:

- i) Improve coordination among health care providers and families;
- ii) Improve children's and parents' quality of life by decreasing the amount of time and effort spent on coordination of care;
- iii) Decrease parental fatigue;
- iv) Improve families' experiences with their child's health care;
- v) Decrease utilization of health services outside the immediate scope of care (i.e., hospital admissions, ER) as a result of improved coordination.

## **2.3 Trial Design**

CCKO will utilize a wait-list variation of a randomized controlled trial design (**Figure 1**). The wait-list approach involves rolling out an intervention over time, whereby all participants are randomized into two groups (A and B) to receive the intervention at different time points determined at random (22,23). Group A would receive the intervention immediately (when resources become available; at time 0). Group B would be on the wait-list and receive the intervention after 12 months. This study design uses the time period before the intervention as the control period/baseline, to be compared in parallel to those receiving the intervention (22). Baseline measurements would be collected at month 0, and Groups A and B would be compared at months 6 and 12.

**Figure 1 – Trial Design**

[figure not shown]

The wait-list design is used in scenarios where it is considered unethical to withhold an intervention or treatment with proven benefits, or if there are logistical or financial constraints that prevent the intervention from being administered at one time point (22,23). This design generates evidence of an intervention program's cost-effectiveness by leveraging real-world operational need for staggered rollout of CCKO to all eligible children for logistical reasons (e.g. high workload for key workers in the first few weeks to months after meeting families in order to create care plans and foster relationships). All CCKO sites intend to deliver care coordination to all eligible children. However given human resource limitations, CCKO program implementation will require the creation of a waitlist in order to be able to include all the patients. With the exception of patients for whom care coordination is urgently required (see exclusion criteria a)-c) in 3.2), all patients referred to CCKO will randomly assigned to either receive the intervention immediately (at the soonest available clinic appointment) or after the waitlist period (1 year). From a research perspective, this approach minimizes the risk of selection bias by retaining the design element of randomization.

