#### Exclusion Criteria:

- a) High Utilization of hospital level care
  - $\geq 3$  hospitalizations,  $\geq 2$  ICU admissions,  $\geq 30$  days of total hospitalization in previous 3 months, excluding newborn admission
- b) Patient with tracheostomy and home ventilation
- c) Medical Status is deemed highly fragile and the need for close follow-up is deemed essential by both referring and triaging team
- d) Already followed by a complex care team
- e)  $>16.0$  years of age
- f) Inadequate English language skills to comprehend study questionnaires
- g) Parent will not be involved in child's care over entirety of study period (2 years)

Patients whose caregivers cannot complete questionnaires in English will not be involved in the primary analysis which involves patient-reported outcome measures (PROMs) and patient-reported experience measures (PREMs) that are written and validated in English, but in order to ensure equitable access to this novel service, they will be allowed to enrol in the clinic and if possible provide health care utilization data via health card linkages at ICES that will be used in secondary analyses. Similarly, we will exclude those patients who are thought to be in need of urgent care coordination by their clinicians (e.g. acuity deemed urgent for care coordination due to new technology such a tracheostomy/ventilation or significant medical complexity with an prolonged inpatient stay), but these patients will contribute data with consent through linkage through their health card to routinely available health administrative data.

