- vi) Health Services Use Among Patients excluded from RCT: A secondary analysis will be performed after completion of the primary trial analysis for children who were excluded from randomization (e.g. those judged to urgently need care coordination), as well as those who cannot complete questionnaires (non-English speaking patients). For such children, we will try to find age- and sex-matched controls in the catchment area of London Health Sciences Centre (where there is no complex care program) with similar patterns of health utilization in the year prior to enrolment and meeting criteria for CMC using an administrative database definition that we have used previously. We will employ a differences-in-differences approach comparing changes in health services utilization and cost, patient- (or caregiver-) reported health-related quality of life, and family functioning, for all children before- and after- intervention, controlling for time trends. Other analyses will also determine which predictor variables distinguish trajectories for at risk groups for future work.
- vii) In addition to a complete case analysis, since it was noted on original analysis that there was substantial missing data, the data were analyzed imputing missing values. Missing primary and secondary outcome data were imputed using multiple imputation by chained equations incorporating baseline variables, group assignment and the corresponding outcomes at baseline and 6 months.

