## **4.0 Ethics and Dissemination**

### **4.1 Research Ethics Approval**

The protocol will be reviewed by Research Ethics Boards at all participating sites. Study participants will be asked to provide written informed consent which will be obtained by the study Research Coordinator at SickKids and Research Assistants at other sites. The study Research Coordinator or Research Assistant will obtain informed consent from parental caregivers. Informed consent/assent will be obtained from all those who are able to provide it. Patients who decline to participate in the collection of PROMs and PREMs will be offered to consent for use of data on health services use from readily available administrative data. Health service data will also be collected on those who are excluded from participating (e.g. due to linguistic barriers or over 16 years old) by waiver of consent.

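### Section 2.3 as worded randomises non-English-speaking children, other sections place them outside the trial, and the one analysis specified for them uses London controls, not allocated arms

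*Protocol*

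**What the plan says.** On who is randomised, section 2.3 (text after Figure 1) opens with the exception, "With the exception of patients for whom care coordination is urgently required (see exclusion criteria a)-c) in 3.2), all patients referred to CCKO", and states the rule: "all patients referred to CCKO will randomly assigned to either receive the intervention immediately" or after one year. Section 3.3 assigns eligible patients at random, and does so before they are approached for consent.

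On language, section 3.2 lists as exclusion criterion f) "Inadequate English language skills to comprehend study questionnaires". It then explains: "Patients whose caregivers cannot complete questionnaires in English will not be involved in the primary analysis", and adds that "they will be allowed to enrol in the clinic and if possible provide health care utilization data via health card linkages at ICES", for use in secondary analyses. Section 3.4 describes the study population as confined to English speakers. Section 4.1 names language, next to age over 16, as a ground for exclusion, and allows health service data on excluded children to be collected under a waiver of consent.

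On analysis, section 3.12, Additional Analyses, item vi is headed as covering patients excluded from the RCT. It takes in children excluded from randomisation, with urgent need as the example, "as well as those who cannot complete questionnaires (non-English speaking patients"). For both groups it plans matched controls from the London catchment and a difference-in-differences analysis.

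On decliners, section 4.1 says: "Patients who decline to participate in the collection of PROMs and PREMs will be offered to consent" to the use of administrative data. The cost analysis in section 3.12, Primary Analyses, item vi is built on health services used by participants.

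**The concern.** The protocol gives two answers to a basic question: whether children under criterion f) are randomised. The answer decides which analysis of their hospital use and cost makes sense.

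If they are randomised, a comparison by allocated arm is available from ICES records and needs no questionnaire. The plan names no such comparison. It names one that depends on how well London children match and on the two regions sharing a trend. Under 1:1 allocation about half of these children would also spend the first year on the wait list, so the before and after periods would start at different dates in the two arms.

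A second gap does not depend on that question. Eligible families are allocated before they are asked for consent, so those who decline the questionnaires already have an arm. If acceptance differs by arm, a cost analysis limited to those who accepted compares groups selected after allocation. Reduced utilisation is one of the stated hypotheses (section 2.2, v), and it can be measured without questionnaires.

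**Working it through.** **The plan's own figure.** Section 3.6 gives 140 children. With a difference of 0.5 SD, two-sided 5% and 80% power: n per arm = 2 × (1.960 + 0.842)² / 0.5² = 62.8, so 63. With 10% loss, 63 / 0.90 = 70 per arm, or 140 in total. The figure reproduces, and the point does not depend on it.

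**The rest is a comparison of texts.**

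1. *Exception in section 2.3.* Section 3.2 has seven exclusion criteria, a) to g). Section 2.3 exempts three, a) to c), from random assignment. The other four, including f), are left inside it.

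2. *Texts that place criterion f) children outside the trial.* Section 3.2 lists f) as an exclusion. Section 3.3 randomises eligible patients only. Section 3.4 limits the population to English speakers. Section 4.1 groups language with age as grounds for exclusion. The heading of Additional Analyses vi says its subjects are outside the RCT.

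3. *Texts that fit section 2.3.* Section 3.2 explains the language exclusion as removal from the questionnaire-based primary analysis. Additional Analyses vi names non-English-speaking patients as a second group, beside those excluded from randomisation; if language already barred randomisation, the separate mention would not be needed.

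4. *What follows under each reading.* If these children are not randomised, no arm exists and an external control is a reasonable choice. If they are, a by-arm ICES comparison is possible and is not specified. Section 3.2 refers only to secondary analyses in general, which neither plans nor rules it out.

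5. *The comparator.* Additional Analyses vi relies on London being without a complex care programme. Section 3.1 says London will take part in CCKO, though not in the evaluation. Nothing says that London's start falls after the comparison period, so control children may be exposed to the intervention.

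6. *Decliners.* Random assignment comes first and consent second (section 3.3), so an eligible family that declines questionnaires has an arm. Section 4.1 offers linkage to such families. The cost analysis refers to participants, and no by-arm analysis that includes decliners is named.

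7. *Precision.* If k linked children were added to 140, with equal variance and balanced arms, the standard error would change by the factor √(140 / (140 + k)). The protocol gives k neither for non-English-speaking children nor for decliners who accept linkage, so the factor cannot be evaluated.

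**The case against.** The best case against is that section 2.3 is a loose summary. Taken literally it would also randomise children already followed by a complex care team (d), those over 16 (e) and those whose parent will not be involved throughout (g). Randomising the first of these to wait for complex care makes no sense. The same paragraph speaks of rollout to eligible children, and the permission to enrol in section 3.2 mentions neither wait list nor allocation. On this view there is no arm to discard. This stands as far as it goes: it makes the reading outside the trial plausible, but it does not remove the contrary wording in sections 2.3 and 3.12.

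A reader might infer that the plan throws away an unbiased comparison for a biased one. The documents do not support that. That these children have an arm is not established. The London analysis matches on age, sex, prior utilisation and complexity and controls for time trends, so bias is a risk and has not been shown. Section 3.2 obtains the ICES data only where possible, so a by-arm set could also be selective, although the waiver in section 4.1 reduces that worry for language exclusions. For decliners, linkage consent comes after allocation and can itself differ by arm.

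A reader might also put a size on the gain. Assuming non-English-speaking children add 10% to 20% to 140 (14 to 28 children) gives √(140/154) = 0.953 and √(140/168) = 0.913, a standard error 5% to 9% smaller; but that share has no source in the protocol. Setting 140 against the pool of 400 in section 3.7 gives √(140/400) = 0.592, or 41%; but the same section expects 50% recruitment, so 200, and √(200/400) = 0.707, or 29%. The pool of 250 in section 3.6 gives √(140/250) = 0.748, or 25%. All three pool figures assume that every non-participant is linked. None is an estimate.

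Finally, a by-arm analysis may be set out in a statistical analysis plan that is not at hand. That could fill the gap on decliners. It would not correct the contradiction within the protocol.

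**Conclusion.** The protocol contradicts itself on whether children under criterion f) are randomised, and it contradicts itself on London, the comparator it assigns them. If section 2.3 is followed as written, the specified analysis is the weaker of two that the planned data allow. If the other sections are followed, an external comparison is reasonable and only the London inconsistency remains.

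The point about decliners holds under either reading. It rests on allocation preceding consent, as section 3.3 states, and on participants in the cost analysis meaning those who joined the evaluation; the protocol does not define the term further.

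The consequence is confined to secondary utilisation and cost results and to whom they apply. No gain in precision and no size of bias can be computed from the documents. The three FECC co-primary comparisons are not affected.

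**What to change.** 1. Reconcile sections 2.3, 3.2(f), 3.3 and 3.12 (Additional Analyses vi) so that all state the same thing about whether criterion f) children are randomised; bring sections 3.4 and 4.1 into line.
2. If they are randomised, analyse their ICES utilisation and cost by allocated arm, stratified by centre, and keep the London comparison for children who were not randomised.
3. Reconcile sections 3.1 and 3.12 on London's status, and state whether London children could have received CCKO during the comparison period.
4. Add an intention-to-treat ICES analysis by arm that includes questionnaire decliners who consent to linkage alongside trial participants. Report the number asked and the number consenting to linkage in each arm, because that consent follows allocation.

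The cost is mainly wording. The linkages are already foreseen in sections 3.2 and 4.1. What is needed in addition is that the allocation of every randomised child, including non-participants, is kept with the linkage file, and that linkage consent is counted by arm.

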## 3.0 Methods

### 3.1 Study Setting

The CCKO evaluation will take place at three pediatric tertiary care children's hospitals (The Hospital for Sick Children [SickKids] Toronto, ON, Children's Hospital of Eastern Ontario [CHEO], Ottawa, ON; Hamilton Health Sciences, Hamilton ON), and their respective satellite clinics (Michael Garron Hospital, Toronto, ON, North York General Hospital, Toronto, ON, Credit Valley Hospital, Mississauga, ON, Peterborough Regional Health Centre, Peterborough, ON, Royal Victoria Hospital, Barrie, ON, Orillia Soldiers' Memorial Hospital, Orillia, ON). These sites were chosen due to their size, relative proximity, spread across Ontario, as well as interest in collaborative work to improve the health of CMC. An additional tertiary care children's hospital, London Health Sciences Centre, will be involved in CCKO, but not in this evaluation. Further sites in Northern Ontario are also anticipated to join CCKO, but will also not be part of this evaluation.

### 3.2 Eligibility Criteria

The target study population includes children who satisfy the Standard Operational definition for CMC who are MFTD living in the catchment area of participating centres. The specific inclusion criteria are summarized in **Figure 2**. Patients will be identified from either practices and/or health care organizations.

#### Exclusion Criteria:

- a) High Utilization of hospital level care
  - $\geq 3$  hospitalizations,  $\geq 2$  ICU admissions,  $\geq 30$  days of total hospitalization in previous 3 months, excluding newborn admission
- b) Patient with tracheostomy and home ventilation
- c) Medical Status is deemed highly fragile and the need for close follow-up is deemed essential by both referring and triaging team
- d) Already followed by a complex care team
- e)  $>16.0$  years of age
- f) Inadequate English language skills to comprehend study questionnaires
- g) Parent will not be involved in child's care over entirety of study period (2 years)

Patients whose caregivers cannot complete questionnaires in English will not be involved in the primary analysis which involves patient-reported outcome measures (PROMs) and patient-reported experience measures (PREMs) that are written and validated in English, but in order to ensure equitable access to this novel service, they will be allowed to enrol in the clinic and if possible provide health care utilization data via health card linkages at ICES that will be used in secondary analyses. Similarly, we will exclude those patients who are thought to be in need of urgent care coordination by their clinicians (e.g. acuity deemed urgent for care coordination due to new technology such a tracheostomy/ventilation or significant medical complexity with an prolonged inpatient stay), but these patients will contribute data with consent through linkage through their health card to routinely available health administrative data.

